### Handling of missing data

Based on the importance of the Bandcizer data, we have planned for how to use the data if we are not able to extract it as planned. Thus, we prioritize to use the Bandcizer data the following way depending on what is possible:

1) As planned with a valid total time-under-tension (TUT) estimate.

2) If 1) is not possible, we will use the total number of repetitions as an estimate of the total exercise dose.

3) If 1) and 2) is not possible, we will use the total number of days with performed exercise as an estimate of the total exercise dose.

We will report the proportion of missing data, e.g. self-reported non-compliance in Bandcizer use or invalid Bandcizer sensor-data. Furthermore, we will perform a sensitivity analysis using data on total exercise dose (days with exercise) from the exercise diary. This will inform if there is a comparable dose-response relationship when analyzing self-reported compliance data compared to objectively measured data (Bandcizer). The two types of data yield a risk of different types of bias. Self-reported exercise dose is often over-estimated and the Bandcizer data may induce problems with missing data as described above which could led to an underestimation of exercise-dose.

Missing items within the HOOS and General Self-efficacy scale will be handled as recommended in the guidelines (HOOS: <50% missing items in each subscale is accepted, self-efficacy: ≤3 missing items is accepted). Concerning ActivPal data, a minimum of four days of data collection will be accepted as sufficient to calculate min/day upright time and steps/day
^41^. In situations where participants have to stop the physical tests due to pain, the data from the best performance are used no matter if the pre-defined number of repetitions is reached. It is noted if tests are interrupted due to pain to be able to perform sensitivity analysis if appropriate. If participants are lost to follow up (despite the before-mentioned efforts to keep every participant in the trial) they will be excluded from the analyses that include change scores. We will not use last-observation-carried-forward or other imputation procedures on exposure (exercise dose), as we aim to investigate relationships between actually performed exercise dose and changes in post-operative outcomes. However, on possible confounding variables that are included in the model, we will use multiple imputation if needed to retain the sample size of n=88 in the analysis. Models used in the imputation will include the remaining confounders with measures as predictors.

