### Primary analysis

Initially, scatterplots of outcome variables and exercise dose variables will be used to suggest starting model structures and possible more complex alternatives. The structures of the models used for the dose-response analysis will depend on the specific relationship between change in gait speed and the exercise dose variable. Because of this, and not having any prior knowledge of the structure of the relationship, multiple models will be fitted and evaluated by R-squared values to identify the models that fit data the best. As a starting point, the first model will be fitted as a fixed increase in outcome, based on exercise dose-change done by linear regression modelling. If necessary, more complex regression such as polynomial relationship and other nonlinear structures will also be evaluated.

In the case that none of the models seem to fit the data, a linear regression model with a categorical variable based on intervals of the exercise dose variable will be fitted. This model does not provide a direct dose response relationship but provides an estimate of the association between the outcome variable and the exercise dose variable within the specific intervals.

“Regression to the mean” may be present and will be evaluated by the correlation between the change and the measure at baseline. If regression to the mean is believed to be present for an outcome, the models of the outcome will additional include the baseline measure to adjust for regression to the mean.

Possible confounding variables (self-efficacy (baseline), physical activity (during intervention), and gait speed (baseline)) will also be included in the models. The confounding effect of each variable will be examined by comparison of dose response estimates in models with and without the confounder. If there is no relevant change between the estimates of the models, the confounder will be excluded from the model. Normality assumptions in the models are evaluated by QQ-plots

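### The imputation model for missing confounders names only the other confounders as predictors; without exercise dose and outcome it dilutes the adjustment, by an amount that depends on how much is missing

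*Protocol article*

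**What the plan says.** The Primary analysis section regresses change in gait speed on exercise dose and lists the adjustment set: "Possible confounding variables (self-efficacy (baseline), physical activity (during intervention), and gait speed (baseline)) will also be included in the models". Whether each variable stays is decided by change in estimate: "The confounding effect of each variable will be examined by comparison of dose response estimates in models with and without the confounder", and "If there is no relevant change between the estimates of the models, the confounder will be excluded from the model".

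Handling of missing data rules out imputation of exercise dose. Of participants lost to follow-up it says "they will be excluded from the analyses that include change scores". For confounders, however, "we will use multiple imputation if needed to retain the sample size of n=88 in the analysis". The imputation model is then specified in one sentence: "Models used in the imputation will include the remaining confounders with measures as predictors". No other section adds dose, outcome or any further variable to it.

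The Secondary analyses section applies the same analysis to change in HOOS ADL.

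**The concern.** An imputation model should contain every variable of the analysis it serves, exposure and outcome included. If a missing activity value is drawn from self-efficacy and baseline gait speed alone, the drawn value is unrelated to dose and to gait change once those two are held fixed. Adding it to the regression then does nothing to remove confounding by activity in that participant.

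Two results are at stake. The first is the primary dose slope. This is a non-randomised cohort, so confounder adjustment is the main protection for its claim of preliminary efficacy. If more active or more confident patients both exercise more and recover faster, the leftover bias favours exercise. The second is the change-in-estimate rule: a diluted confounder moves the dose estimate too little, so a real confounder is more easily judged irrelevant and removed.

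**Working it through.** **1. The planned effect.** Sample size gives 0.2 m/sec over a 4-hour dose range, an SD of 1.06 h for dose and of 0.16 m/sec for change in gait speed, power 0.90 and alpha 0.05 (two-sided assumed). The slope is 0.2/4 = 0.05 m/sec per hour. Standardised, it is 0.05 × 1.06/0.16 = 0.331. A t-based calculation for a slope with residual SD 0.16 × √(1 − 0.331²) gives 87.3, hence 88: the planned figure is reproduced. A standardised bias converts to m/sec over 4 hours by the factor 4 × 0.16/1.06 = 0.604.

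**2. Which values would be imputed.** A participant without baseline gait speed has no change score and leaves the primary analysis. That leaves self-efficacy and activity. For activity, "a minimum of four days of data collection will be accepted as sufficient", so fewer days means a missing value. Every analysed record has an observed outcome, and an observed dose wherever the sensor data are valid, so both can serve as predictors.

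**3. One confounder, closed form.** Assumptions: a standardised confounder has correlation r with both dose and outcome, the true dose effect is zero, and a share p is missing completely at random and replaced by draws unrelated to both. Dose and outcome then correlate r², and the completed confounder correlates (1 − p)r with each. The dose slope adjusted for it, which is pure bias, is

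bias = r²[1 − (1 − p)²] / [1 − (1 − p)²r²].

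Example, r = 0.4 and p = 0.2: 0.16 × 0.36 / (1 − 0.64 × 0.16) = 0.0576/0.8976 = 0.064.

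| Missing (assumed) | Bias, r = 0.4 (m/sec over 4 h) | Bias, r = 0.3 (m/sec over 4 h) |
|---|---|---|
| 5% | 0.018 (0.011) | 0.010 (0.006) |
| 10% | 0.035 (0.021) | 0.018 (0.011) |
| 20% | 0.064 (0.039) | 0.034 (0.021) |
| 30% | 0.089 (0.053) | 0.048 (0.029) |
| 40% | 0.109 (0.066) | 0.060 (0.036) |

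Simulation at n = 88 (1,500 datasets, 10 imputations) agrees for r = 0.4: 0.016 at 5%, 0.04 at 10%, 0.06 at 20% and 0.11 at 40%.

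**4. Three confounders, simulation.** Set-up: n = 88, a true adjusted effect of about 0.20 m/sec over 4 hours, and one of three mutually correlated confounders missing completely at random. Estimates are in m/sec over 4 hours.

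| Missing | Weak confounding: confounders only | Stronger: full data | Stronger: confounders only | Stronger: plus dose and outcome |
|---|---|---|---|---|
| 5% | 0.200 | 0.198 | 0.205 | 0.198 |
| 10% | 0.202 | 0.202 | 0.214 | 0.202 |
| 20% | 0.206 | 0.202 | 0.226 | 0.203 |
| 40% | 0.208 | 0.202 | 0.243 | 0.204 |

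The share of the omitted-confounder bias that remains is about 11%, 21%, 39% and 68% at 5%, 10%, 20% and 40% missing. Among imputed records, the partial correlation of the confounder with dose given the others is 0.00; for the true values it is 0.15 (weak) or 0.34 (stronger). Complete-case analysis was unbiased in these runs.

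**5. Effect on the change-in-estimate rule.** In the setting of step 3 with r = 0.4, full adjustment moves the dose slope by r² = 0.16. With the diluted confounder it moves by 0.16 − 0.018 = 0.142 at 5% missing, 0.16 − 0.064 = 0.096 at 20% and 0.16 − 0.109 = 0.051 at 40%. The article sets no threshold for a relevant change, so the chance of wrong exclusion cannot be computed.

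**The case against.** The sentence says what the imputation models will include. It does not say that nothing else enters, and its wording is unclear. A condensed article may leave a fuller model to a plan that is not shown. A reader might therefore infer too much by saying that dose and outcome are deliberately excluded; the text does not establish that. What remains is that this is the only specification given, in an article whose abstract says that it includes the statistical analysis plan. An analyst who followed it would leave both variables out.

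A reader might also infer that the dose estimate will be biased whatever happens. The documents do not support that either. Imputation is used only if needed, ActivPAL requires four of seven days, and the self-efficacy scale tolerates up to three missing items, so missingness may be low. At 5% and 10% missing with r = 0.4, simulated type I error was 0.051 and 0.057, and the bias was roughly 0.1 to 0.4 of a standard error (about 0.11). It rose to 0.087 at 20% and 0.144 at 40%. Under weak confounding the estimate on the trial's scale was at most 0.208 against 0.20. This limits the size of the problem but does not make the rule sound, and the rule is fixed before missingness is known.

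The refusal to impute exercise dose is no answer, because using observed dose as a predictor does not impute it. Baseline gait speed, as one of the predictors, carries some information on the outcome but does not restore the missing link to dose.

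**Conclusion.** The point holds conditionally. As written, the imputation model omits the exposure and the outcome of the model that it serves, so imputed confounder values adjust only for what the other confounders already carry. The leftover bias is minor at 5% to 10% missing or with weak confounding. It becomes material at 20% to 40% missing with correlations near 0.4: 0.06 to 0.11 in standardised units, or 0.04 to 0.07 m/sec over 4 hours against a planned 0.2. With correlations of 0.3 it is 0.03 to 0.06 standardised over the same range.

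The missing shares, the correlations and the completely-at-random mechanism are all assumptions; the article gives none of them. Under that mechanism the planned imputation brings in a bias that dropping the incomplete records would avoid. The weakening of the change-in-estimate rule follows from the same mechanism, but how often a true confounder would be dropped is not established.

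**What to change.** Replace the sentence on imputation predictors with one stating that, for each analysis, the imputation model includes exercise dose, the outcome of that analysis and all confounders. The outcome is change in gait speed for the primary analysis and change in HOOS ADL for the HOOS ADL analysis; naming gait speed alone would repeat the fault in the second. State that dose and outcome serve as predictors only and are not themselves imputed, which keeps the existing rules on exposure and loss to follow-up intact. Auxiliary variables are optional at n = 88; dose and outcome alone removed the bias in the check above.

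Report the share missing for each confounder, and a complete-case analysis as a sensitivity analysis. The cost is a sentence or two in the plan, a small change to the code and one additional model fit for each outcome. No new data are needed.

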### Data monitoring

Since the study involves no major changes to current practice it is not deemed necessary to establish a data monitoring committee or perform any interim analyses. Likewise, no provisions for post-trail care will be made.

## Discussion

This trial will add knowledge concerning the preliminary efficacy of home-based rehabilitation using elastic band exercises based on the relationship between performed exercise dose and outcomes after THA. We believe this is the first trial to do so, since earlier attempts have not used objective measurement of exercise dose as in the present trial. In an observational cohort study, Zech
*et al.* found no significant associations between the exercise therapy intensity or duration and improvements in patient reported function, pain, and stiffness
^42^. However, the exercise dose was dependent on the participants´ health insurance as well as individual conditions and the physiotherapist's decision, which likely induces a risk of bias by indication.

The essential need from a clinical perspective is to be able to prescribe evidence-based exercise programs after THA. Despite the growing number of studies, a recent systematic review that included 20 studies concludes that insufficient therapeutic validity and potentially high risk of bias in the included studies limit the ability to assess the effectiveness of exercise after THA
^43^.

The new knowledge from the present study can potentially identify whether the dose of performed home-based exercise is related to changes in post-operative outcomes after THA. It will give insight concerning the potential influence from other factors than exercise, such as general physical activity and self-efficacy. Furthermore, the embedded qualitative study will give insight to perceived motivation and barriers to perform the prescribed exercise as well as to resuming general physical activities. The results from both the quantitative and qualitative study are expected to be useful in optimizing current practice; however, the results will also be used to plan, power and execute a randomized controlled trial that compares the effectiveness of rehabilitation exercises to no rehabilitation exercises (just resuming general physical activities).

### Strength and limitations

The strengths of this study include the objectively measured exercise dose, the standardized and thoroughly described intervention and the inclusion of outcome variables at all levels in the
International Classification of Function, Disability and Health (ICF). We chose gait speed measured by the 40-m fast-paced walk test as the primary outcome. Walking ability is considered the most important function to improve by patients undergoing THA surgery
^25^, and the 40-m fast-paced walk test is part of the core set of functional tests to include in clinical trials in patients with osteoarthritis in hip or knee recommended by OARSI
^26^. An important candidate for the choice of primary outcome for clinical research has been suggested to be a patient-reported one
^44^. Nevertheless, we chose a performance-based measure as the primary, as we were concerned about ceiling effects on patient reported outcomes that measures function and pain, such as the HOOS questionnaire after THA
^45^.

Multiple factors can potentially affect exercise compliance; therefore, we include measurements of physical activity and self-efficacy. Also, it is not known which outcomes that is most susceptible to exercise dose which is why we include a broad range of different outcome types to be able to explore potential dose-response relationships.

Blinding of participants in randomized exercise trials are often impossible, in the present study we seek to blind the participants to the specific focus om exercise dose, they are just told that we measure "the way they exercise". Hypothesis blinding is considered a design strength when blinding of participants regarding treatment is not possible
^46^. Furthermore, we blind the outcome assessor in the sense that they are not allowed to see the exercise diary or BandCizer data prior to the outcome assessment.

## Trial status

The trial began recruiting participants in April 2017. After a period with slow inclusion, the inclusion rate is back at 1–2 participants per week, thus, inclusion is expected to be completed in July 2019. See current status on participant flow in
Figure 1.

This paper is based on protocol version 5, March 8, 2019.

## Declarations

### Research ethics approval

The Ethics Committee of Central Denmark Region accepted initiation of the study and reviewed the study as non-notifiable (Inquiry 270/2017). The study was approved by the Danish Data Protection Agency (ref. no: 1-16-02-589-15).

### Informed consent

Trained Research staff (nurse or physiotherapist) will provide presentation of comprehensible information about the research to potential participants, confirmation that they understand the research, and assurance that their agreement to participate is voluntary. Potential participants will also receive information sheets. They will be offered deliberation time and, subsequently, written consent will be obtained from those who choose to participate. The informed consent document is available as
*Extended data*
^20^.

### Confidentiality

All records that contain names or other personal identifiers, such as informed consent forms, will be stored separately from study records identified by code number to protect confidentiality before, during, and after the trial.

### Future availability of trial data

The principal investigator, as well as all co-authors, will have access to the full dataset as needed. A fully anonymized dataset and statistical analysis code will be made available for the scientific journal reviewing the manuscript within six months in line with the recent proposal from the International Committee of Medical Journal Editors (ICMJE)
^47^.

### Dissemination policy

Results from the trial will be published in international, scientific peer-reviewed journals, no matter the trial outcome. The results will also be presented at relevant scientific conferences and symposiums. Authorships will be allocated according to the
ICMJE recommendations. The following papers are planned:

1. Pragmatic Home-Based Exercise after Total Hip Arthroplasty – Silkeborg (PHETHAS-1): Results from a prospective cohort study.2. Motivation and barriers to perform home-based exercise after Total Hip Arthroplasty – a qualitative embedded study within the PHETHAS-1 trial.

## Data availability

### Underlying data

No underlying data are associated with this article.

### Extended data

Figshare: PHETHAS-1 protocol.
https://doi.org/10.6084/m9.figshare.8256014
^20^.

This project contains the following extended data:

WHO Trial Registration Data Set_PHETHAS.docxConsent document.pdfManaging pains associated with exercise.docx (pain management guide)PHETHAS Interview guide_english (PHETHAS-2 interview guide, translated into English)Questionnaire_ Motivation to perform exercises.docxQuestionnaire_Evaluation of prescribed exercises.docxCERT Checklist.docxTIDieR Checklist.docx

Extended data are available under the terms of the
Creative Commons Zero “No rights reserved” data waiver (CC0 1.0 Public domain dedication).

### Reporting guidelines

Figshare: SPIRIT checklist for “Pragmatic Home-Based Exercise after Total Hip Arthroplasty - Silkeborg: Protocol for a prospective cohort study (PHETHAS-1)”.
https://doi.org/10.6084/m9.figshare.8256014
^20^.
